### Interventions

#### ICBT – the PTSD program

The PTSD program consists of six online lessons in the form of a cartoon narrative that contains best practice CBT as well as regular homework assignments and access to supplementary resources. Lesson summaries and skills practice homework assignments are available for download by participants following each lesson. Homework tasks encourage practice of the skills covered in each lesson (see Table 2). The program is completed over 10 weeks. Participants will be encouraged to complete the program within this time and receive automated reminders to progress. There will be a 5-day minimum interval from completing one lesson before the next is accessible to encourage skills practice before continuing. However, participants can choose to log in at any time beyond this. Participants can also choose the duration they spend on each lesson and skills practice. Participants are encouraged to spend 3–4 hours per week on lesson content and associated skills practice. An outline of key skills and resources covered across the PTSD program is provided in Table 2. Lessons are followed by skills practice assignments completed independently by patients throughout the iCBT program. This model has strong empirical support for the effective treatment of depression, GAD, SP, PD with and without agoraphobia, and mixed anxiety and depression [62], and is already used by our online treatment service, THIS WAY UP Clinic at St Vincent’s Hospital Sydney, Australia. Courses for the treatment of these other disorders are currently available to patients and, to date, over 5000 patients have completed a course.

**Table 2 Tab2:** Skills and additional resources covered over the posttraumatic stress disorder (PTSD) program by lesson

Lesson	Skills	Extra resources
1	• Psychoeducation on PTSD diagnosis and treatment	• Managing mood • Sleep • Information for family and friends
2	• Psychoeducation: o How avoidance maintains PTSD o Fight-or-flight response o Cognitive behavioural model of PTSD o About cognitive behavioural therapy (CBT) • Controlled breathing	• Progressive muscle relaxation • Structured problem solving
3	• Link between thoughts and feelings • Thought monitoring • Psychoeducation for written exposure and practice of writing a trauma narrative	• Labelling emotions
4	• Psychoeducation and practice on reading the trauma narrative • Thought challenging	• Identifying and challenging thoughts in key themes (e.g. safety, trust)
5	• Behavioural experiments • Situational exposure • Continued writing and review of the trauma narrative	• Assertive communication • Extra information for family and friends • Attention shifting
6	• Key skills review • Relapse prevention	None

### Participant monitoring

The Clinical Trials Manager of CRUfAD and a member of the research team will oversee participant monitoring. Symptom severity of the target disorder and general distress levels are measured before, during, and immediately upon completing the PTSD program based on empirically validated standardised internet-delivered symptom measures. Participants will be sent automated emails at the completion of each lesson to encourage skills practice. Patient queries throughout the program are primarily addressed by email contact from the clinician (AA) or the Clinical Trials Manager (JS). If clinically indicated, or if a patient’s K10 and/or PHQ9 or PCL-C scores deteriorate, the clinician makes telephone contact. If a participant misses a lesson, a member of the research team will send an email reminder (via the Virtual Clinic system) or will make telephone contact to remind the participant to complete the lesson.

The treatment group will be required to complete the iCBT program within 10 weeks to remain in the trial. Adherence is monitored throughout the program. Once enrolled, a participant can elect to discontinue at any time. A participant may be withdrawn from the trial (typically meaning course access will be closed) for the following reasons: lack of computer and internet access; change in prescribed medication for anxiety or depression; change in medication status of exclusion medications; suicidality or clinical risk; failure to complete baseline questionnaires; failure to commence the PTSD program. Lack of adherence throughout the iCBT program is not a specified reason for participant withdrawal, although a participant may withdraw voluntarily. Those in the waitlist control group will be required to complete questionnaires at weeks 1, 5 and 11 of the waitlist period to remain in the RCT. The waitlist control group will have access to the iCBT program immediately at the conclusion of the waitlist period. All reasons for withdrawal status will be documented.

To promote participant retention, participants are reminded that data collection is an important aspect of research and enables the research team to track their progress and to evaluate the program. Any adverse events will be reported to the Director of CRUfAD (GA) and to the Human Research Ethics Committee (HREC) of St Vincent’s Hospital, the responsible body for initiating a clinical trial audit.

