**Methods/Design:**

Patients with PTSD will be recruited via the research arm of a not-for-profit clinical and research unit in Australia and randomised to a treatment group or waitlist control group. The minimum sample size for each group (alpha 0.05, power 0.80 for a *g* of 0.47) was identified as 72, but 10 % more will be recruited to hedge against expected attrition. PTSD diagnosis will be determined using the PTSD module from the Mini International Neuropsychiatric Interview version 5.0.0. The PTSD Checklist – Civilian version (PCL-C) will be used to measure PTSD symptoms (the primary outcome measure), with the Intolerance of Uncertainty Scale 12-item version (IUS-12) and the Emotion Regulation Questionnaire (ERQ) used to measure intolerance of uncertainty and emotion regulation, respectively. The PCL-C will be administered to the treatment group before each lesson of the PTSD program and at 3-month follow-up. The IUS-12 and ERQ will be administered before lessons 1 and 4, at post-treatment and at 3-month follow-up. The waitlist control group will complete these measures at week 1, week 5 and week 11 of the waitlist period. PTSD program efficacy will be determined using intent-to-treat mixed models. Maintenance of gains will be assessed at 3-month follow-up. Mediation analyses using PROCESS will be used to examine the association between change in PTSD symptoms over treatment and change in each of IU and emotion regulation ability in separate analyses.

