### Primary outcome measures

Administration time points for all instruments are contained in Table 1.

**Table 1 Tab1:** Administration time points for questionnaires used in the RCT

	Administration time point				
Measure	Pre-treatment	Before each lesson	Mid -treatment^d^	Post-treatment^e^	3-month follow-up^f^
LEC^a^	♦				
DES	♦				
MINI	♦				♦
PCL-C^b^	♦	♦	♦	♦	♦
BDI-II^c^	♦		♦	♦	♦
PHQ-9	♦		♦	♦	♦
K10	♦	♦	♦	♦	♦
GAD-7	♦		♦	♦	♦
CEQ	♦			♦	
IUS-12	♦		♦	♦	♦
ERQ	♦		♦	♦	♦
SUDOR	♦		♦	♦	♦
SAPAS	♦				

*LEC* Life Events Checklist, *DES* Dissociative Experiences Scale, *MINI* Mini International Psychiatric Interview, *PCL-C* PTSD Checklist **–** Civilian version, *BDI-II* Beck Depression Inventory – Second Edition, *PHQ-9* Patient Health Questionnaire 9-item version, *K10* Kessler Psychological Distress Scale 10-item version, *GAD-7* Generalised Anxiety Disorder 7-Item Scale, *CEQ* - Credibility and Expectancy/Satisfaction Questionnaire, *IUS-12* Intolerance of Uncertainty Scale 12-item version, *ERQ* Emotion Regulation Questionnaire, *SUDOR* Service Utilisation and Days Out of Role Questionnaire, *SAPAS* Standardised Assessment of Personality - Abbreviated Scale

^a^Refers to both LEC-IV and part 2 of LEC-5

^b^Includes items 10, 11, and 16 from PCL-5

^c^Item 9 only

^d^Waitlist control group completes these measures at week 5 of the waitlist period

^e^Waitlist control group completes these measures at week 11 of the waitlist period

^f^Treatment group only

**Posttraumatic stress disorder Checklist – Civilian version** (PCL-C) [40]. The PCL-C is a 17-item self-report questionnaire providing a continuous measure of PTSD symptomatology, conforming to Diagnostic and Statistical Manual of Mental Disorders, Fourth Edition (DSM-IV) diagnostic criteria. Each item reflects a PTSD symptom and is rated on a 5-point scale for distress (1 = “Not at all”; 5 = “Extremely”). Items 10, 11 and 16 from the PCL-5 [41] will also be administered, which assess new diagnostic criteria for PTSD in the fifth edition of the DSM [DSM-5 1]. This approach was adopted in favour of sole use of the PCL-5, which had not been validated at the time of trial design. This will enable examination of change in the new PTSD symptoms in DSM-5.

**PTSD diagnostic status**. Change in PTSD diagnostic status will be indexed using the MINI PTSD module. The MINI has sound reliability and validity psychometrics [39].

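### Outcome timing follows lesson progress in the iCBT arm and calendar weeks on the waitlist, so elapsed time at the primary endpoint can differ by arm, and no endpoint assessment is stated for iCBT non-completers

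*Protocol article*

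**What the plan says.** **iCBT arm.** Participant monitoring ties assessment to progress through the course: "Symptom severity of the target disorder and general distress levels are measured before, during, and immediately upon completing the PTSD program". The Abstract (Methods/Design) says of the PCL-C: "The PCL-C will be administered to the treatment group before each lesson of the PTSD program and at 3-month follow-up". Of the two mechanism scales it says: "The IUS-12 and ERQ will be administered before lessons 1 and 4, at post-treatment and at 3-month follow-up". Under Interventions, pacing is left to the participant: "There will be a 5-day minimum interval from completing one lesson before the next is accessible", followed by "However, participants can choose to log in at any time beyond this".

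**Waitlist arm.** The Abstract gives calendar times: "The waitlist control group will complete these measures at week 1, week 5 and week 11 of the waitlist period". The footnotes to Table 1 repeat this for the mid-treatment column ("Waitlist control group completes these measures at week 5 of the waitlist period") and the post-treatment column ("Waitlist control group completes these measures at week 11 of the waitlist period"). Neither footnote gives a week for the iCBT arm, although both arms share the two columns.

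**Staying in the trial.** Participant monitoring requires the iCBT arm to finish the program inside 10 weeks in order to stay in the trial. It requires the waitlist to complete its questionnaires. The same paragraph says that poor adherence to the program is not a specified ground for withdrawal.

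**Endpoint and analysis.** The Objectives make the end of treatment the primary endpoint. Statistical methods plans intent-to-treat mixed models (REML) to handle drop-out, plus a separate analysis of those who complete all six lessons.

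**The concern.** Two things are at stake.

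First, the labels mid and post mean a stage of the course in one arm and a date in the other. If the model treats them as common time points, part of the between-arm contrast reflects elapsed time rather than treatment. Within the iCBT arm, elapsed time also depends on how fast each person works.

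Second, a measurement triggered by completing the program has no stated trigger for someone who stops at, say, lesson 3. The before-lesson PCL-C stops at the same point. Waitlist participants have no such dependency. Loss of the primary endpoint would then fall in one arm and follow treatment progress. An intent-to-treat estimate most needs outcome data from exactly these participants, and analysis cannot recover data that were never collected.

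**Working it through.** **1. The plan's own figure.** With g = 0.47, two-sided alpha 0.05 and power 0.80 (sidedness is not stated, but two-sided reproduces the figure):

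n = 2 × (1.960 + 0.842)² / 0.47² = 71.1, rounded up to 72 per group.

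This matches the article. A 10% increase gives 72 × 1.10 = 79.2, so 80 per group. The sample size is not in dispute.

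**2. Permitted timing.** Inputs are the 5-day minimum gap (Interventions), the 10-week limit (Participant monitoring) and waitlist weeks 5 and 11 (Table 1 footnotes). Assumptions: lesson 1 is day 0, each lesson takes one day, and week k covers days 7k − 6 to 7k. The iCBT mid-treatment point is taken as before lesson 4, as the Abstract gives it for the IUS-12 and ERQ.

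| Point | iCBT earliest | iCBT latest | Waitlist |
|---|---|---|---|
| Mid | 3 × 5 = day 15 | 70 − 2 × 5 = day 60 | week 5: days 29–35 |
| Post | 5 × 5 = day 25 | day 70 | week 11: days 71–77 |

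- Post, fastest pace: 71 − 25 = 46 to 77 − 25 = 52 days apart, about 6.6 to 7.4 weeks.
- Post, full 10 weeks: 71 − 70 = 1 to 77 − 70 = 7 days apart.
- Mid at an even pace: lesson 4 at day 35 (six equal slots, 3 × 70/6) or day 42 (five equal intervals, 3 × 70/5), close to week 5.

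**3. What a timing gap could be worth.** The documents give no waitlist trajectory. Assume linear waitlist improvement of 0.1 to 0.2 SD over the 70 days from week 1 to week 11, and that every iCBT participant finishes on day 25:

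- Share of the period: (70 − 25)/70 = 0.643.
- Drift: 0.643 × 0.1 to 0.2 = 0.064 to 0.129 SD, which is 14% to 27% of 0.47.
- If the average gap is half the maximum, this is about 7% to 14%.

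On this assumption the waitlist has had longer to recover when it is measured, so the contrast is shrunk and the bias runs against iCBT. If the waitlist worsens, the sign reverses.

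**4. What missing endpoints could cost.** The documents give no iCBT non-completion rate, so the rates below are assumed. They apply to a simple post-treatment comparison with 80 randomised per arm and no endpoint value for non-completers. Power = Φ(0.47/√(1/m + 1/k) − 1.96), where m and k are the numbers with an endpoint in the iCBT and waitlist arms.

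| iCBT non-completion | Power, no waitlist loss | Power, 10% waitlist loss |
|---|---|---|
| 10% | 0.825 | 0.805 |
| 20% | 0.800 | 0.781 |
| 30% | 0.770 | 0.751 |
| 40% | 0.731 | 0.713 |
| 50% | 0.680 | 0.664 |

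A mixed model that uses earlier scores would recover some of this precision. Selective loss is the larger worry. With no outcomes observed after stopping, non-completers' endpoints are in effect projected from those who continued.

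**The case against.** Several points against the concern have force.

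- **The arms need not diverge.** The program is described as a 10-week course with reminders, and waitlist weeks 5 and 11 fit that length. A reader might infer that the arms are always measured at different elapsed times. The documents support only that they can be; day 25 requires every lesson to be taken at the minimum gap.
- **Non-measurement is not stated.** A reader might infer that iCBT non-completers are never measured at the endpoint. No sentence says so. Table 1 lists the PCL-C at post-treatment without limiting it to completers, an intent-to-treat analysis is planned alongside a completer analysis, and a condensed article may omit how stoppers are followed up. What stands is that the only stated trigger is completion, and that the retention rule refers to the program in one arm and to questionnaires in the other.
- **The 14% to 27% figure is a ceiling.** It rests on an assumed drift and on the whole arm finishing at the fastest pace, so it should not be read as an expected bias.
- **Empty cells are conjecture.** It is tempting to say that the before-lesson scores leave group-by-time cells with no waitlist counterpart. The article does not say how time is coded or whether those scores enter the between-arm model. That may properly be left to an analysis plan.
- **The mixed model helps.** If before-lesson scores are used, participants who stop still contribute under missing at random, and predictors of drop-out are to be examined. This reduces the problem but does not remove it: a regression of drop-out on observed variables cannot detect dependence on outcomes nobody saw.

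**Conclusion.** The concern holds in a limited form. The article fixes a progress-triggered schedule in one arm and a calendar schedule in the other under shared labels. Elapsed time at the primary endpoint can therefore differ by up to about 7 weeks, and by almost nothing for those who use all 10 weeks. The documents do not allow the bias to be sized. Its direction depends on the waitlist's course, and it is against iCBT if the waitlist improves.

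The weightier part is the endpoint for iCBT participants who do not finish. It appears to be unscheduled, though this is a strong inference rather than stated text. The statements on completing within 10 weeks and on non-adherence conflict and must be reconciled. The day counts rest on the conventions given above, and the power figures on assumed non-completion rates. This is a cheap and worthwhile correction, not a fatal flaw.

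**What to change.** Send the online outcome battery to every randomised iCBT participant at week 5 and week 11, matching the waitlist, whatever lesson has been reached and whether or not the participant still uses the program. Base the between-arm primary contrast on these common time points. Keep the before-lesson and end-of-program scores for monitoring and for description within the iCBT arm. Reconcile the Participant monitoring statements on remaining in the trial, and state that not completing the program does not end outcome collection.

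The costs are modest: two scheduled online prompts, a little more questionnaire burden, and no visits or extra staff. There are two real drawbacks. For fast finishers the primary time point falls some weeks after completion (about 46 to 52 days at the extreme), which changes what end of treatment means for them and should be stated. Participants already enrolled may also have been assessed only on the present schedule; 26 had met eligibility at submission, against 2 × 72 = 144 needed. The report should say how many were assessed under each schedule.

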### Participants and recruitment

Participants will be recruited through flyers, paid print and internet advertising. Applicants will first complete online screening questionnaires about symptoms and demographic details (see Fig. 1 for a participant flow chart). Inclusion criteria are as follows: meet diagnostic criteria for PTSD; computer, internet and printer access; Australian resident; fluent in written and spoken English; willing to provide name, phone number and address, and to provide the name and address of a local general practitioner. Exclusion criteria are as follows: trauma occurrence within the past 4 weeks; non-resident of Australia; less than 18 years of age; currently receiving treatment for trauma/PTSD; frequent suicidal ideation (indicated by a score of 3 to item 9 of the Patient Health Questionnaire 9-item version (PHQ9)); regularly using illicit drugs or regularly consuming more than three standard drinks per day; psychotic disorder or taking atypical antipsychotics or benzodiazepines; if taking medication for anxiety or depression, has been taking the same dose for less than 1 month or intending to change the dose during the course of the program; currently highly dissociative (indicated by score ≥40 on the Dissociative Experiences Scale as per Spence et al. [20]); current or pending medicolegal proceedings associated with the reported trauma; applying for, or receiving, Workers Compensation associated with their trauma or PTSD. Excluded applicants will receive information on alternative services and will be encouraged to discuss their symptoms with their physician. Applicants who pass the screening phase will be telephoned for a diagnostic interview using the PTSD module from the Mini International Neuropsychiatric Interview version 5.0.0 (MINI) [39] to determine whether they meet diagnostic criteria for PTSD. All interviews will be conducted by a registered Clinical Psychologist (AA) or Clinical Trials Manager (JS) under the guidance of the Clinical Psychologist and trained in administration of the diagnostic interview. Applicants who satisfy all inclusion criteria will be informed of the study design and will complete an electronic informed consent prior to enrolling in the trial. Information from the diagnostic interview will be used for research purposes only for those participants who provide informed consent. All participants will be informed in writing that they may withdraw from the study (i.e. choose to cease program enrolment or choose for their data to be excluded from the RCT) at any time without jeopardising their relationship with St. Vincent’s Hospital or the University of New South Wales. Further, those participants randomised to the waitlist control group will be informed that should they commence a trauma-focused intervention outside of the trial, their data will be omitted from the RCT.

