### Statistical methods

Power calculations were informed by calculation of effect size data from Spence et al. [20], providing a between-group effect corresponding to Hedges’ g of 0.47. The minimum sample size for each group (alpha set at 0.05, power at 0.80) was identified as 72, but at least 10 % more will be recruited to hedge against expected attrition. All analyses will be conducted at conclusion of the trial period (i.e. after all participants in the treatment group have completed the iCBT program). Significance testing of group differences regarding demographic data and pre-treatment measurements will be conducted using analysis of variance (ANOVA) and χ2 where the variables consist of nominal (or categorical) data. Intent-to-treat (ITT) mixed models using restricted maximum likelihood (REML) estimation will be used to account for missing data due to participant drop-out. Mixed models do not assume that the last measurement is stable (the last observation carried forward assumption) [63]. REML models are appropriate for RCTs with multiple time points and pre-to post-only designs [64]. The assumption that data are missing at random (MAR) will be evaluated using binary logistic regression to predict drop-out (0 = no drop-out, 1 = drop-out) and by comparing these two groups on baseline measures. Significant effects will be followed up with pairwise contrasts comparing mean pre-treatment to mean post-treatment scores. Complete-case analyses of the primary hypotheses using data from participants who complete all six lessons of the PTSD program will also be conducted. The effect of potential treatment moderators (e.g. time post-trauma, number of traumatic events) will be evaluated by including baseline variables of interest as a covariate and interaction term in separate mixed models analyses. Analyses will be performed in IBM SPSS version 21. Effect sizes will be calculated between groups (Hedges’ g) and within groups (Cohen’s d, adjusting for the repeated measures correlation) using the pooled standard deviation and adjusted for sample size.

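### The Participant monitoring section makes staying in the trial depend on program completion (iCBT) or questionnaire return (waitlist), which conflicts with its own withdrawal rules and puts post-treatment assessment of non-finishers at risk

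*Protocol article*

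**What the plan says.** All references are to the protocol article.

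**Participant monitoring, retention conditions.** For the iCBT arm: "The treatment group will be required to complete the iCBT program within 10 weeks to remain in the trial". For the waitlist arm, participants are "required to complete questionnaires at weeks 1, 5 and 11 of the waitlist period to remain in the RCT".

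**Participant monitoring, withdrawal.** The list of reasons opens with "A participant may be withdrawn from the trial (typically meaning course access will be closed) for the following reasons". It includes never starting the program but not failing to finish it or finishing late. The paragraph then adds: "Lack of adherence throughout the iCBT program is not a specified reason for participant withdrawal, although a participant may withdraw voluntarily".

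**ICBT – the PTSD program.** On the same 10 weeks: "Participants will be encouraged to complete the program within this time".

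**Statistical methods.** "Intent-to-treat (ITT) mixed models using restricted maximum likelihood (REML) estimation will be used to account for missing data due to participant drop-out". Drop-out is also to be modelled by logistic regression, and drop-outs compared with the rest at baseline, to examine the missing-at-random assumption. Separately: "Complete-case analyses of the primary hypotheses using data from participants who complete all six lessons of the PTSD program will also be conducted".

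**Participants and recruitment.** Voluntary withdrawal is described as one of two things: stopping the program, or asking for one's data to be left out. Where loss of data is meant for another reason, the text says so. Waitlist participants are told that "should they commence a trauma-focused intervention outside of the trial, their data will be omitted from the RCT".

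**Timing of the post-treatment assessment.** The Objectives section makes the end of treatment the primary endpoint. Table 1 (footnote e) fixes that assessment at week 11 for controls. For the iCBT arm, Participant monitoring places it directly after the program is completed, and no calendar date is given.

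**The concern.** Finishing a program and returning a questionnaire both happen after randomisation, and both may be related to how the participant is doing. If either becomes a condition of staying in the trial, the people still being assessed at the end are no longer the groups that were randomised. Here the condition also differs by arm: treatment completion on one side, data completion on the other.

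The primary endpoint is what is at stake. A participant who has done some of the lessons by week 10 is someone whose post-treatment PCL-C an intent-to-treat comparison needs. If staff treat that person as out of the trial, the score is never collected, and no later analysis decision can recover it. In the waitlist arm, a control who misses week 5 and is then treated as out would lose the week 11 score as well. A single missed visit, which the mixed model can handle, would become a missing endpoint.

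**Working it through.** The point turns on wording. It disputes no figure in the plan, so the check is to apply each rule to the same cases.

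**Case A: an iCBT participant who has reached lesson 4 at the end of week 10.**

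1. Retention sentence (Participant monitoring): the program is not complete within 10 weeks, so the participant does not remain in the trial.
2. Withdrawal list (same paragraph): neither late nor incomplete completion is listed, so there is no ground for withdrawal.
3. Adherence sentence (same paragraph): non-adherence is not a specified reason, so the participant stays.
4. Intervention section: finishing in 10 weeks is encouraged, so the participant stays.
5. Statistical methods: the model is intent-to-treat and meant to handle drop-out, so the participant is analysed with whatever data exist.

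Rule 1 gives one answer and rules 2 to 5 give the other.

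**Case B: a waitlist participant who misses the week 5 questionnaire but would answer at week 11.**

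1. Retention sentence: one of the three required questionnaires is missing, so the participant does not remain in the RCT.
2. Withdrawal list: a missed questionnaire after baseline is not listed, so there is no ground for withdrawal.
3. Statistical methods: incomplete series are what the REML mixed model is there to handle, so the participant stays.

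**Does the document show that data would be removed from the analysis?** It does not:

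- A regression predicting drop-out, coded 0 or 1, can be fitted only if drop-outs are in the dataset.
- A separate analysis of six-lesson completers adds something on the iCBT side only if non-completers are in the main analysis.
- Participants and recruitment separates stopping the program from excluding data.
- The one stated rule for omitting data on grounds other than the participant's own request, for outside treatment in the waitlist arm, says so openly. The two retention sentences do not mention data.
- Table 1 has the PCL-C completed before each lesson, so a non-finisher already has several scores that the model can use.

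**What does the analysis section leave unrepaired?** The end-of-treatment score itself:

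- Control: week 11, fixed by footnote e of Table 1.
- iCBT participant who finishes: on completion of the program.
- iCBT participant who does not finish: no completion event, so nothing in the stated schedule prompts the assessment.

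A mixed model can use the earlier scores of such a participant, but only under the missing-at-random assumption. It cannot replace an endpoint that was not sought.

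**The case against.** A reader might infer that non-finishers are dropped from the analysis, so that the intent-to-treat result becomes a completer result in the iCBT arm, with a biased effect and lost power. The document does not support that. The drop-out regression, the mixed model for drop-out, the separate completer analysis and the distinction between leaving the program and excluding data all indicate that collected data stay. A power calculation based on removed participants would model an exclusion that is not planned, so none is given here.

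The other side can go further:

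- **The rules may coexist.** Non-adherence could mean slow or missed lessons within the window, with 10 weeks as the end of the window, and encouragement fits a fixed end date. This is a fair reading of what may have been intended. It does not remove the conflict, because the retention sentence speaks of remaining in the trial and not of access to the course.
- **Withdrawal usually means closed access.** The protocol says so, and this supports an access-only reading. But the remark is attached to listed reasons that do not include lateness, so it does not clearly govern the 10-week sentence.
- **An article condenses.** How off-program participants are followed up, and the exact analysis set, may be in a fuller protocol or analysis plan. That is accepted, and silence on those details is not the point. The point is that the article states a retention rule, in each arm, that contradicts other rules it also states.
- **The fixed-date questionnaire is a new procedure in a running trial.** This is true, but the measures are already delivered online and the added work is small.

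**Conclusion.** The concern holds as a badly stated conduct rule. The two retention sentences conflict with the withdrawal rules in the same paragraph, with the encouragement wording in the intervention section, and with the intent-to-treat plan. If staff follow them literally, assessment stops for randomised participants on post-randomisation criteria that differ between arms, and non-finishers in the iCBT arm lose the post-treatment PCL-C.

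Exclusion of collected data from the analysis is not shown, and the Statistical methods section points the other way.

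The size cannot be given. The document has no figure for how many participants would be unfinished at week 10 or would miss a waitlist questionnaire, nor for how their outcomes differ. Neither the magnitude nor the net direction of any bias follows from it. The risk depends on one assumption: that staff take the retention sentences at their word. If they already treat the 10 weeks as an access limit and keep assessing everyone, the defect is one of wording, apart from the missing assessment date for non-finishers.

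This is a cheap improvement: low cost, and worth making because an uncollected endpoint cannot be recovered later.

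**What to change.** In Participant monitoring:

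1. Delete the clause that makes 10-week completion a condition of staying in the trial, and state that the 10-week limit governs course access only.
2. Replace the waitlist condition with a request to complete the questionnaires at weeks 1, 5 and 11.
3. Send the online post-treatment measures to every iCBT participant who has not finished, at a fixed date aligned with the controls' week 11, and still invite them to the 3-month follow-up.
4. State that neither condition removes anyone from follow-up or from the intent-to-treat model, subject to withdrawal of consent.

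The encouragement wording and the six-lesson completer analysis can stay. The rule on outside treatment in the waitlist arm is a separate matter and is not changed here.

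The cost is two wording changes, one clarifying statement and a little extra questionnaire follow-up. According to Trial status, 26 participants had met eligibility at submission. The planned minimum is 72 × 1.10 = 79.2, so 80 per arm or 160 in all, and most of the trial can therefore run under the clear rule. Anyone already treated as out under either condition should be documented and, where consent allows, kept in the analysis with the data they gave.
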